## Abstract

**Background:**

Neuropathic pain is a complex chronic pain condition often accompanied by affective symptoms such as anxiety and depression. This comorbidity is associated with increased pain severity, disability, and diminished quality of life, complicating treatment. Virtual reality (VR) is an innovative non-pharmacological intervention that is gaining attention for its potential to alleviate pain and anxiety through immersive distraction. The Protocol Committee of the University of Salamanca (Spain) has approved the study protocol (approval code: ID.1243)

**Objective:**

We aimed to evaluate the efficacy of VR in reducing pain and anxiety in patients with persistent neuropathic pain.

**Methods:**

This randomized, controlled, multicenter, open-label trial involves two groups: an intervention group receiving VR sessions and a control group receiving standard pharmacological treatment. Participants are adults aged 30‐61 years diagnosed with neuropathic pain, unresponsive to flexible doses of gabapentin. Pain and anxiety levels are assessed using the Pain Detect Questionnaire, Visual Analog Scale (VAS), and Goldberg Anxiety Scale at baseline and follow-up points. VR sessions are conducted weekly for 3 weeks, each lasting 30‐35 minutes. Perceived time during VR sessions is recorded as an indirect measure of distraction effectiveness. The primary outcome is the reduction in pain intensity and anxiety levels post-intervention compared to baseline. A sample size of 30 patients (15 per group) was calculated to achieve 80% statistical power, considering a 2-point mean difference in VAS scores.

**Results:**

A preliminary pilot study was completed with 16 patients, including 9 who received the virtual reality intervention. Initial findings showed reduced pain perception in 3 patients and decreased anxiety in 4 patients. These results informed the current protocol, which is scheduled to begin in 2025 and is currently in the preparatory phase.

**Conclusions:**

This study hypothesizes that VR will significantly reduce pain and anxiety in patients with persistent neuropathic pain. By providing new insights into non-pharmacological pain management strategies, this research aims to enhance the quality of life for these patients. The findings could support the broader application of VR in clinical pain management.

## Introduction

Pain is defined as a complex and multidimensional sensory experience that includes cognitive, behavioral, and psychological elements, often associated with unpleasant and subjective experiences. It has an adaptive function that initiates protective responses. Neuropathic pain is a form of chronic pain resulting from injury to the peripheral or central nervous systems. It is characterized as pain directly caused by an injury or disease affecting the somatosensory system [1].

Neuropathic pain frequently coexists with affective symptoms and negative emotions (anxiety, depression, fear, etc). It is estimated that 20%‐30% of patients with chronic pain also experience anxiety-depressive symptoms. Specifically, 50% of patients with chronic pain experience major anxiety-depression at some point, with 34% in the case of neuropathic pain [2,3].

The comorbidity of chronic pain and affective disorders is closely associated with higher pain severity, greater disability, and a substantial decline in patient quality of life [4], complicating treatment significantly. Persistent long-term pain and associated suffering seem to be key factors in developing secondary affective and emotional disorders. Long-term neuropathic pain has been shown to hyperactivate the LC-BLA pathway (that increases the activity of projections from the locus coeruleus [LC] to the basolateral amygdala [BLA]—a key noradrenergic circuit involved in arousal, emotional memory, and stress-related behaviors), responsible for anxiety symptoms secondary to the pain process [5].

Treating neuropathic pain is challenging. Pain management programs, therapeutic education, and physical training are fundamental for improving this type of pain. Therefore, it is crucial for patients to understand their pain process to change erroneous beliefs about it, as difficult-to-treat neuropathic pain is related to various psychosocial factors such as high stress or anxiety levels and various emotions caused by the pain.

Techniques aimed at reducing pain and anxiety are being introduced. One non-pharmacological, safe, and innovative technique that could potentially reduce pain and anxiety and is gaining interest in the scientific community in the “new technologies era” is virtual reality (VR). VR findings have helped to better understand the underlying processes of pain experiences and the analgesic role such strategies can play [6].

VR provides a three-dimensional, multisensory, and immersive environment that allows individuals to have modified reality experiences by creating a sense of “presence,” making it an excellent candidate for distraction-based therapy. This is suggested to decrease attention to painful stimuli, which could affect the emotional interpretation associated with it, thus reducing perceived intensity.

Distractions help reduce anxiety by preventing painful stimuli from being transmitted to the thalamus (ie, the limbic system) or the sensory cortex as effectively, helping to focus attention on external and internal stimuli rather than nociceptive stimuli. Sometimes, distractions surpass the capability of local anesthetics to control pain and discomfort associated with medical interventions. Distractions can be active (immersive), involving patient participation by manipulating the environment, or passive (non-immersive), involving only observation [7].

Current technological advances, especially in the field of VR, have resulted in new types of distractions that can be used alongside traditional distractions to achieve better pain control in patients.

In VR technology, users interact with a computer-simulated three-dimensional environment. VR provides multisensory information (visual, auditory, tactile, and olfactory stimuli) that helps individuals interact in the simulated world. A literature review by Lopez-Valverde et al [8] concluded that VR has shown its utility in reducing chronic pain and related issues such as anxiety, hopelessness, time spent thinking about pain, and perceived time during a procedure.

The concept of “virtual reality” lacks a unique and homogeneous definition among authors who have worked on it. We believe the most appropriate definition is by Riva [9], who conceptualized VR as a communication interface based on interactive three-dimensional visualization capable of collecting and integrating different datasets into a single realistic experience. Various theories have been proposed regarding pain-modulating effects to explain VR’s effects. To understand VR-induced hypoalgesia mechanisms, it is necessary to integrate neurobiological and neurochemical interactions with cognitive-attentional and affective-emotional aspects of the “painful experience” [10].

One of the main hypotheses states that humans have a limited capacity to pay attention to stimuli, so experiencing pain requires some attention to it [11]. Additionally, patients with both acute and chronic pain may experience excessive attention and vigilance towards pain, potentially increasing perceived intensity (or sensitivity to painful stimuli). VR could have an analgesic effect by distracting from the pain focus [12], producing a pain modulation response via neurophysiological activity in brain areas related to analgesia.

However, distraction is not the only proposed effect. The neuromatrix theory suggests that the pain experience results from a complex interaction between attentional, neurobiochemical, and emotional factors specific to each person. Therefore, pain depends on the interpretation and response of the brain matrix. In this context, VR could promote intercortical analgesia by modulating attentional and emotional networks, stimulating areas related to pain inhibition.

Many aspects remain unclear; however, VR use for pain treatment has shown significant benefits.

This study protocol aims to evaluate the outcomes in terms of pain and anxiety relief with VR application in this group of patients with persistent neuropathic pain.

## Methods

### Ethical Considerations

This study will adhere to the principles outlined in the Declaration of Helsinki and has been approved by the Institutional Review Board of the participating centers (University of Salamanca: approval code: ID.1243). Written informed consent (Multimedia Appendix 1) will be obtained from all participants before study enrollment.

### Study Design

#### Trial Design

We will conduct a randomized, controlled, multicenter, open-label, parallel-group trial with two assigned groups (intervention group and control group).

#### Scope and Study Period

The study population will include adults aged 30 to 61 years. The study was started by the beginning of 2025, as shown in Figure 1.

**Figure 1. F1:**
[figure not shown]
Temporal planning of the activity development during the project. VAS: visual analog scale; VR: virtual reality.

### Participants

All patients will be evaluated and deemed suitable by a specialist in the Pain Unit. Neuropathic pain diagnosis was made using the Pain Detect Questionnaire [13].

Neuropathic pain symptoms and signs will be assessed, including sensitivity alterations history such as tingling, numbness, stabbing, burning, shooting, or electric-like pain, paresthesia, allodynia, hyperalgesia, hyperpathia, and motor dysfunction (foot or wrist drop, symmetric motor weakness, difficulty buttoning a shirt or holding a pencil), myalgia, or muscle cramps. Neurological assessment included motor evaluation (muscle strength in limbs), sensory evaluation (touch, pain [pinprick test], cold, heat, vibration, and position, and allodynia test for dynamic and static mechanical stimuli), balance test, coordination, and deep tendon reflexes.

After diagnosing persistent neuropathic pain, oral gabapentin treatment will be prescribed up to 1200 mg/day.

### Inclusion Criteria

Patients will be included if they have moderate to severe pain intensity despite treatment with flexible doses of gabapentin for 3 months up to 1200 mg/24 h, understand VR operation and use of validated scales, and sign informed consent forms (Informed consent available as appendix).

### Exclusion Criteria

The exclusion criteria include known hypersensitivity to gabapentin, inability to tolerate 1200 mg/24 h doses (dizziness and drowsiness), pregnant or lactating women, any relative or absolute contraindication to VR treatment, patients with unstable or poorly controlled hypertension, recent cardiovascular events (6 mo) before starting treatment, long-term diabetics with cardiovascular autonomic neuropathy, elderly patients, or those with cognitive deficits who cannot understand or apply the scales or answer the questions correctly.

### Randomization

#### Sequence Generation

Randomization will be performed using the RandomizedR computer system (CRAN-R Project), a randomization tool in the R Studio program.

#### Implementation

Participants will be selected from a daily patient registry. Both the sequence and participant assignment to interventions will be generated by the RandomizedR computer system.

#### Masking

Due to the study’s nature, it will not be possible to blind patients or health care professionals. Therefore, the trial will be open-label. However, a third-party blind evaluation will be conducted, as the data analysis responsible will not be involved in the intervention.

### Data Collection, Sources of Information, and Intervention

Pain intensity will be measured using the PainDETECT Questionnaire [13], which is self-administered with 9 descriptors. It detects neuropathic pain intensity and discriminates between possible neuropathic pain (scores between 12 and 19) and definite neuropathic pain (scores above 19). The Visual Analog Scale (VAS) is a one-dimensional quantitative, effective, and easily reproducible scale. Patients mark a 100-mm segment with endpoints labeled as no pain (0 mm) and maximum pain (100 mm); the measure from 0 to the patient-marked point indicates pain intensity. A change of 20 mm (or 2 points on a 10-point pain intensity scale) is considered clinically significant.

Anxiety will be measured using the Goldberg Anxiety Scale [14], a test that not only guides diagnosis but also measures intensity. It contains 2 subscales with 9 questions each: anxiety subscale (questions 1‐9). The first 4 questions of each subscale (questions 1‐4) act as a precondition to determine if the rest of the questions should be answered. Specifically, if fewer than 2 questions of the first 4 are answered affirmatively, the rest of the first subscale questions should not be answered. For the second subscale, it is sufficient to answer one of the questions 10‐13 affirmatively to proceed with the rest of the questions.

Time perception will be analyzed as an indirect measure of distraction, with less attention to pain, greater tolerance, and possibly an early sensation of completing the treatment time (or Tprogrammed).

At the end of each VR session (30 to 35 minutes), patients will be asked how much time they think remains. This is called “perceived time” (Tperceived) and will be recorded in 10‐15-minute intervals based on their responses.

A “significant” difference is defined as a time difference (Tprogrammed - Tperceived) of ≥15 min and “no change” if ≤10 min. For patients who request to stop before completing the time, their “perceived time” is noted by adding the remaining time to the total programmed time.

The frequency and duration of the intervention—fifteen 30-minute VR sessions over 3 consecutive weeks (Monday to Friday)—were selected based on previous studies demonstrating that repeated short-duration sessions enhance user immersion and treatment adherence without inducing fatigue or diminishing attention [15]. This schedule allows for progressive desensitization to pain stimuli and anxiety reduction through consistent exposure to immersive distraction.

For the VR application, the Oculus Go VR 32GB (Meta) model was used, featuring a head-mounted display. This headset provides a stereo visual image, thereby creating a sense of space and depth. A motion tracker in the headset’s screen measures head position and adjusts the visual image accordingly. As a result, users perceive their surroundings and can move through the simulated environment. The headset is accompanied by headphones that provide sounds, further enhancing the user’s immersion in the virtual world.

Participants in the control group underwent the usual pain assessment review during the 2-week study period.

Eligible patients will be invited to participate in the study continuously, and the assignment to study groups will be randomized.

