## Results

The current study began in April 2025 and is currently in the preparatory phase. Previously, a preliminary pilot study was conducted in which 16 patients were recruited, of whom 9 received the VR intervention [16].

In this pilot study, using a distraction chosen by each participant, a significant reduction in pain (defined as a decrease of ≥2 points on the VAS compared to previous experience) was observed in 3 patients. Five patients reported no noticeable change (VAS difference of 0 or 1 points), and 1 patient experienced worsening symptoms and discontinued participation.

Additionally, anxiety, measured using the Goldberg Scale, decreased during the session in 4 patients, with “significant anxiety” defined as a score >2 points.

Regarding time perception, 50% of participants reported a notable difference in their perception of time passage 30 days after the intervention (considered significant if the treatment duration was perceived as 30 min).

These preliminary results provided the rationale for the current full-scale randomized controlled trial, which aims to evaluate whether the use of virtual reality is effective in reducing anxiety and chronic neuropathic pain. In the current protocol, a statistically significant reduction in heart rate and pain intensity in the intervention group compared to the control group will be considered a satisfactory outcome.

If the hypotheses are confirmed, this intervention could be implemented in routine care and extended to other procedures involving difficult-to-manage pain.

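### The perceived-time question asks for time remaining, but the scoring rule fits only time elapsed; taken literally, the ends of the distraction scale swap

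*Protocol article*

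**What the plan says.** All the elements stand in the Protocol article, Data Collection, Sources of Information, and Intervention. Time perception is introduced there as a proxy for distraction.

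- **Question.** When a session of 30 to 35 minutes ends, "patients will be asked how much time they think remains".
- **Definition.** The next sentence reads: "This is called “perceived time” (Tperceived) and will be recorded in 10‐15-minute intervals based on their responses".
- **Scoring.** A 'significant' difference "is defined as a time difference (Tprogrammed - Tperceived) of ≥15 min"; a difference of 10 minutes or less is 'no change'.
- **Early stoppers.** For a patient who asks to stop before the time is up, perceived time "is noted by adding the remaining time to the total programmed time".

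The Abstract presents perceived time as the indirect indicator of how well the distraction works, and Patient Selection lists it with the VAS and Pain Detect scores to be analysed. Nowhere does the article convert time remaining into time elapsed.

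**The concern.** If Tperceived is the time the patient thinks is left, subtracting it from the programmed time returns the time the patient felt had passed. A large difference then means that the session felt long, or was judged accurately. A small one means that it felt short, which is what distraction should produce. The labels run the other way.

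At stake is the trial's evidence on mechanism. Followed to the letter, the plan could report strong distraction where there was none and no change where it was strongest. The trial is multicenter, so some sites might ask about time remaining and others about time elapsed. The pooled answers would then mix two opposite scales, and this could not be reliably undone unless the wording used was recorded with each answer.

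**Working it through.** No sample size or error rate is involved. The check applies the stated rule to possible answers.

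**Inputs**, all from Data Collection, Sources of Information, and Intervention:
- T = Tprogrammed = 30 or 35 min.
- R = time the patient thinks remains, asked at the end of the session.
- E = time the patient feels has elapsed. I assume the patient knows the programmed length, so E = T − R.
- D = T − Tperceived; 'significant' if D ≥ 15, 'no change' if D ≤ 10.

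**Two readings**
- As written: Tperceived = R, so D = T − R = E.
- As a duration: Tperceived = E, so D = T − E = R.

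**T = 30 min**

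| R | E | D as written | Class | D as duration | Class |
|---|---|---|---|---|---|
| 0 | 30 | 30 | significant | 0 | no change |
| 5 | 25 | 25 | significant | 5 | no change |
| 10 | 20 | 20 | significant | 10 | no change |
| 15 | 15 | 15 | significant | 15 | significant |
| 20 | 10 | 10 | no change | 20 | significant |
| 25 | 5 | 5 | no change | 25 | significant |
| 30 | 0 | 0 | no change | 30 | significant |

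**T = 35 min.** As written, R = 0, 5, 10, 15 and 20 give D = 35, 30, 25, 20 and 15, all 'significant'; R = 25, 30 and 35 give D = 10, 5 and 0, all 'no change'. As a duration, R = 0, 5 and 10 give D = 0, 5 and 10, 'no change'; R = 15 and above give D ≥ 15, 'significant'.

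**Where the readings agree.** Both give 'significant' when R ≤ T − 15 and R ≥ 15. That is R = 15 only for T = 30, and R from 15 to 20 for T = 35.

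**No time distortion.** Every patient has R = 0. As written, D = T (30 or 35), so 100% are 'significant'. As a duration, D = 0, so none are.

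**Early stoppers.** I take the remaining time as the scheduled time not completed. Stopping at 20 of 30 min gives Tperceived = 30 + 10 = 40 and D = 30 − 40 = −10, 'no change'. In general D is minus the unused time, so it is always negative. A Tperceived of 40 min cannot be time left in a 30-minute session, so this rule presupposes a duration. Combined with the literal question, it puts early stoppers in the same class as the patients who felt least time pass.

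**Recording.** The cut-offs are 15 − 10 = 5 min apart, while answers are kept in intervals of 10 to 15 min. For T = 30, an elapsed estimate stored as 15 to 25 min covers D from 30 − 25 = 5 to 30 − 15 = 15, which touches both classes and the unlabelled band between them.

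**The case against.** The best defence is that only one phrase is wrong. The difference, both cut-offs and the early-stop rule all fit a felt duration, and the labels then follow the distraction rationale. The question may be a slip for how much time has passed, and the actual item would sit in the Microsoft Forms questionnaire, which is not shown. This largely stands. It locates the fault in the question and not in the formula, and it makes the swap conditional on staff using the printed wording. It does not remove the mismatch, because question, definition and formula are all stated and do not fit together.

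Other points also stand. On a duration reading, the early-stop rule is a cautious imputation that classes no early stopper as distracted, although the value is assigned and not perceived. The band between 10 and 15 minutes could be a deliberate indeterminate zone, and answers in multiples of five never fall in it with T of 30 or 35. The article does not say which is meant.

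Three stronger readings are tempting and not supported:
- *The scale is inverted for every patient.* Some mid-range answers get the same label either way.
- *The efficacy results are compromised.* The Abstract's primary outcome is pain and anxiety. The comparisons in Data Analysis and Statistical Analysis cover heart rate, pain, anxiety and satisfaction. Perceived time is in none of them.
- *The pilot scored accurate estimates as distraction.* In Results, the pilot finding was "considered significant if the treatment duration was perceived as 30 min". That would be an accurate estimate only if pilot sessions lasted 30 minutes, and the article does not give their length.

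**Conclusion.** The point holds as a mismatch between the question and its scoring rule. On the printed wording the two ends of the scale swap at both session lengths, and a sample with no time distortion would be classed entirely as 'significant'. This rests on two assumptions: that staff ask the question as printed, and that patients judge time remaining against the programmed length. If the form in use asks for elapsed time, the labels are right and only the article's text needs correcting.

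The coarse recording and the unexplained 10-to-15-minute band are smaller faults in the same rule. This should be fixed, but it concerns a secondary measure taken only after VR sessions and does not touch the estimates of treatment effect on pain or anxiety.

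**What to change.** 1. Ask at the end of the session how many minutes the patient thinks it lasted. Define Tperceived as that elapsed estimate and keep Tprogrammed − Tperceived.
2. Record the answer in minutes, not in 10-to-15-minute intervals.
3. State how differences above 10 and below 15 minutes are classed, even if only as indeterminate.
4. Report early stoppers separately, since their value comes from arithmetic and not from what they perceived.
5. Check that the questionnaire at every site carries the same wording.

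Asking controls a matching question and analysing the difference as continuous would be useful, but both are optional and not needed to correct the error.

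The cost is one reworded question, a short definition and a check of the electronic form. Results describes the trial as in its preparatory phase, so the change can still be made before data accumulate.

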#### Data Collection, Information Sources, and Intervention

Data collection will begin once the patient has provided written informed consent. Patient assignment to a study group will be randomized using the RandomizedR computer system.

The data collector will record the patients’ age, sex, study group, and type of intervention performed. Before contacting the patient with the virtual reality device, the patient’s status and heart rate will be recorded upon arrival at the clinic, regardless of the assigned study group.

Patients in Group 1 will be the intervention group. They will undergo 10 virtual reality pain treatment sessions (Monday to Friday for 2 weeks), with each session lasting 30 minutes, while maintaining treatment with gabapentin at a dose of 1200 mg/24 h. Their clinical history, pain situation, and anxiety will be assessed in each session.

Patients in Group 2 will be the control group. Their clinical history, pain situation, and anxiety will be assessed in each session. They will receive pain treatment with oral gabapentin at a dose of 1200 mg/24 h. The control group will receive standard care without any VR exposure. Participants will remain in a quiet room with standard analgesic treatment as prescribed. No additional relaxation stimuli will be provided. Outcome data will be collected in parallel with the intervention group.

Figure 2 shows the CONSORT diagram.

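### The VR schedule is given as weekly for 3 weeks, 15 sessions over 3 weeks and 10 sessions over 2 weeks, against a 2-week control period, so neither the dose nor the post-intervention time point is defined

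*Protocol article*

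**What the plan says.** The VR schedule appears in three places in the current text.

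- **Abstract, Methods:** "VR sessions are conducted weekly for 3 weeks", with sessions of 30–35 minutes.
- **Data Collection, Sources of Information, and Intervention:** "fifteen 30-minute VR sessions over 3 consecutive weeks (Monday to Friday". This section also defends that frequency and duration by reference to earlier studies.
- **Data Collection, Information Sources, and Intervention** (under Patient Recruitment for Study Participation), in the procedure for Group 1: "They will undergo 10 virtual reality pain treatment sessions (Monday to Friday for 2 weeks), with each session lasting 30 minutes".

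For controls, the section that gives VR 3 weeks also says: "Participants in the control group underwent the usual pain assessment review during the 2-week study period".

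On assessment times, the abstract says only that the scales are completed "at baseline and follow-up points". The group procedures add, for each group, "Their clinical history, pain situation, and anxiety will be assessed in each session", and for controls, "Outcome data will be collected in parallel with the intervention group".

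**The concern.** The three schedules describe the same item in the same trial and cannot all be true. None comes from an amendment log. None describes the pilot, which the Results section reports separately. Condensing a longer protocol can explain missing detail, but it cannot explain different numbers for one quantity.

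Two things are at stake.

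1. **Dose.** The trial is multicentre. If centres follow different parts of the text, patients under one treatment label receive different exposures, and a result could not be attributed to a defined course of VR.
2. **Outcome timing.** The abstract's primary outcome is the change in pain and anxiety from baseline to after the intervention, and the Statistical Analysis section compares the groups by t test. If the end of the intervention is week 3 for VR and week 2 for controls, that comparison confounds treatment with elapsed time and with the number of clinic contacts. The outcomes are self-reported and the trial is open-label, so unequal contact is a credible source of bias.

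**Working it through.** No sample size, power or alpha figure is involved. The check is arithmetic on each stated schedule, followed by a comparison with the control period.

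**Inputs.** Sessions per week, number of weeks and minutes per session, from the three places cited. The abstract gives no session count, so its figure of 3 is inferred from one session a week.

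**Formulas.** Sessions = sessions per week × weeks. Exposure = sessions × minutes per session.

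| Source | Sessions | Exposure | VR ends |
|---|---|---|---|
| Abstract | 1 × 3 = 3 | 3 × 30 to 3 × 35 = 90–105 min | week 3 |
| Group 1 procedure | 5 × 2 = 10 | 10 × 30 = 300 min | week 2 |
| Intervention rationale | 5 × 3 = 15 | 15 × 30 = 450 min | week 3 |

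Each version agrees with itself, so none shows itself to be a slip in a single digit that a reader could correct.

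**Ratios.**
- The two explicitly counted versions: 450 / 300 = 1.5.
- Rationale against abstract: 450 / 105 = 4.3 to 450 / 90 = 5.

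**Timing against the control period of 2 weeks.**
- If the Group 1 procedure governs, both arms end at week 2 and the difference is 0.
- If the 15-session version governs and controls keep 2 weeks, the VR arm ends 3 − 2 = 1 week later. By week 2 it has had 5 × 2 = 10 sessions, so 15 − 10 = 5 sessions fall after the control period has ended.
- If the abstract's version governs and controls keep 2 weeks, the VR arm again ends 1 week later.

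**Assessments.** Pain and anxiety are to be recorded at every session, so the number of assessments (3, 10 or 15) and the date of the last one both depend on which version is used. The text shown gives no day or week for the post-intervention assessment that would settle the matter.

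**The case against.** The conflict between 15 sessions over 3 weeks and 10 over 2 weeks cannot be argued away. The objections concern what is built on it.

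- **The abstract may be loose wording.** It never states 3 sessions, and weekly could be shorthand for the 3-week course. This stands in part. One session a week is the plain meaning, but the 4.3- to 5-fold ratio rests on that reading. The explicit contradiction is 1.5-fold.
- **The arms may be meant to match.** The 2-week wording can be read as the period of the whole study, which fits the Group 1 procedure. Both groups are assessed at each session, controls wait in a quiet room, and control outcomes are to be collected in parallel. On that reading both arms end at week 2 with similar contact. This is fair, and it makes the arm difference conditional. It does not remove it: two of the three statements give VR 3 weeks, and collecting data in parallel does not say which duration applies.
- **Divergence between centres is not shown.** Sites may work from a fuller protocol. This also stands: it is a possible consequence, not something the article states.
- **A visit schedule may exist elsewhere.** Figure 1, captioned as the temporal plan, is not shown, and an article may leave visit days to the full protocol. The point therefore does not rest on missing visit days. It rests on stated durations that conflict, which leave the end of the intervention with more than one meaning.
- **The problem is an inconsistency, not a poor design choice.** Agreed. No schedule is criticised on its merits.

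**Conclusion.** The concern holds and should be corrected before the trial proceeds. The text gives incompatible schedules for the sole experimental intervention, and following it as written cannot produce one dose or one post-intervention time.

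The certain part is 15 sessions over 3 weeks (450 minutes) against 10 over 2 weeks (300 minutes). With the abstract read as one session a week, the range is 90–105 to 450 minutes. The one-week difference in end of treatment between arms arises only if VR runs 3 weeks while controls keep 2. Mixed exposure across centres arises only if sites follow different statements. Analysis could not repair either problem after data collection.

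The document does not show which schedule was intended.

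**What to change.** 1. The sponsor's clinical team chooses one schedule: sessions per week, number of weeks and minutes per session. The abstract, the intervention section and the Group 1 procedure should then state it identically. Session length also needs settling, since it is 30–35 minutes in some places and 30 in others.
2. The rationale in the intervention section should support the chosen schedule. At present it defends 15 sessions, while the Group 1 procedure delivers 10.
3. Replace the 2-week wording for controls with the same period as the VR arm.
4. Define baseline, end of treatment and follow-up by days from randomisation, identical in both arms, and name the day of the primary comparison.

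**Cost.** This is amendment wording only, provided no patient has been enrolled. The Results section says that the study began in April 2025 and is still being prepared, and Scope and Study Period puts the start at the beginning of 2025, so enrolment status should be confirmed first. If the chosen schedule has more sessions than sites have planned for, visits and staffing would also change. If patients have already been treated, the schedule each one received needs to be recorded.
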